***Table 2 – Goal directed targets***

| **Parameter** | **Target** | **Intervention** | **Test of intervention** |
| --- | --- | --- | --- |
| Timing of clinical assessment | Medical review <1 hour of arrival | Training in recognition of the symptoms and signs of meningitis and rapid triage | Timed and signed flow chart |
| Antibiotic therapy | 1^st^ dose within 1 hour of arrival | Education of importance of antibiotics, sepsis flow chart | Timed drug chart |
| Glucose | BM >4 | S/L , NG or IV dextrose | Repeat BM |
| Oxygenation | Sp02 >94% | Nasal flow 02 from concentrator  Packed red cell Transfusion if significant anaemia (Hb 6.0g/dL) | Regular Sp02 monitoring |
| Perfusion | CRT<2 sec, BP >90 syst, MAP >70, no postural hypotension (lying-sitting)/  UOP>0.5ml/kg (if catheterised | IV fluid bolus 20ml/kg Ringer’s lactate where available. | Repeated fluid balance assessment at 1hour then repeated |
| Seizures | No seizures | Acute prompt treatment of seizures with IV/PR benzodiazepines and IV phenytoin if seizures persist | Seizure chart |

***Table 3- Definition of clinical shock***

| **General variables** | **Hemodynamic variables** | **Organ dysfunction variables** | **Tissue perfusion variables** |
| --- | --- | --- | --- |
| Heart rate >90 bpm | Arterial hypotension (SBP <90 mm Hg | Acute oliguria (urine output <0.5 mL/Kg/hr **or** <45 ml/hr for at least 2 hrs (if catheterised)/ no urine production for 12 hours despite adequate fluid resuscitation) | Decreased capillary refill (>3 seconds) |
| Tachypnea RR>25 | MAP <70 mm Hg | Ileus (absent bowel sounds) | Skin mottling |
| Altered mental status | SBP decrease >40 mm Hg |  |  |

All interventions are part of routine accepted care for critically ill patients at QECH, however they are incompletely implemented and are currently not target driven.

**iv.ii Endpoints**

***Primary***

Proportion of each clinical target achieved by the bundle

Total proportion clinical targets when combined together, achieved by the bundle

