**Inclusion criteria**

- Adults ≥14 years age
- Fever/history of fever plus one of:

1. Coma
2. Severe Headache
3. Nuchal rigidity
4. Seizures
5. Confusion

The diagnosis of ABM will be based at presentation on clinical symptoms and signs. A formal diagnosis of ABM will be made following CSF analysis using the following criteria: ***CSF WCC >50 cells/mm^2^ (predominantly neutrophils), visible bacterial seen in the counting chamber irrespective of cell count***, ***positive Gram’s stain*** or culture/PCR positivity for any bacteria known to cause meningitis.

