**iv. i Intervention design**

EGDT will be delivered using a clinical care bundle, based on the ‘ABCD’ approach to resuscitation which has been developed and validated by the American and UK resuscitation councils (24) and consists of eight components, all of which are currently available in QECH and all of which are recognised existing clinical treatments which have supportive evidence of efficacy. The individual components of the bundle can be seen in table 1.

Staff training will form an important component of bundle delivery during phase 2a and ongoing through phase 2b, but will not form a specific bundle element. This is due to difficulties in assessing staff training when no formalised resuscitation training is available that is appropriate to resource limited settings.

The duration of the intervention will be 6 hours from initial screening to the point at which attempts to meet all targets have been achieved. Each subject will receive hourly observations including GCS scoring, blood pressure and pulse measurements. A lumbar puncture for the diagnosis of ABM will be performed at the earliest opportunity.

Study nurses and a clinical officer will deliver the bundle following training, using defined targets (table 2) within the AETC. At the end of the 6 hour study period, the bundle will stop, and the subject will be transferred to the medical ward for ongoing routine care. A flowchart of the study process is available in the appendix 9.

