***Table 1 – Bundle components***

| **Bundle components** |
| --- |
| Naso-pharyngeal airway if GCS <8  Head up/bed tilt 30° if GCS <11  IV access, 2g Ceftriaxone stat  Oxygen via concentrator if SpO2 <93%  IV fluid (Ringer’s Lactate) bolus 20ml/kg if clinical shock, 125ml/hr if no clinical shock (table 3)  Transfusion of packed red cells if haemoglobin <6.0g/dL  Correction of hypoglycaemia with oral dextrose and drinks/food if GCS >11, or with iv dextrose 10-50% via a bolus/infusion if GCS <11  Prompt treatment seizures  *(IV diazepam/lorazepam plus phenytoin for persistent fits/status epilepticus)* |

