**The following statistical tests will be used to compare the intervention and control groups.**

- Composite analysis of each proportion of target achieved
- Simple mortality proportions
- Kaplan-Meir survival analyses to establish the pattern of the death rate
- Chi squared tests and Fisher’s exact test will be used to analyse the significance of differences between the two phases of fixed endpoints.
- Logistic regression will be used to give an estimate of the size of the change in outcomes.
- Where appropriate the students T test and the Mann-Whitney test of medians will be used to compare the outcome between the bacterial loads in blood and CSF.

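### The primary endpoints count patients already at target on arrival as bundle successes for four of the six targets, which inflates attainment and dilutes the comparison between phases.

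*Protocol*

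**What the plan says.** Section iv.ii Endpoints gives two primary endpoints: "Proportion of each clinical target achieved by the bundle" and "Total proportion clinical targets when combined together, achieved by the bundle". Neither has a denominator, an assessment time or a unit of analysis (patient or target). The Data analysis section repeats that a percentage attained will be calculated for each target, again without restricting who is counted. Its list of methods for comparing the groups gives the targets "Composite analysis of each proportion of target achieved"; chi-squared and Fisher's exact tests are a separate item, for fixed endpoints.

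Table 2 has six rows. Two are process times: medical review within an hour and, for antibiotics, "1^st^ dose within 1 hour of arrival". Four are states: glucose above 4, saturation above 94%, a set of perfusion criteria, and no seizures. Table 1 makes most of the matching treatments conditional, for example "Oxygen via concentrator if SpO2 <93" (per cent). Section iv.i says that the bundle "consists of eight components, all of which are currently available in QECH", so six targets stand beside eight components.

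Seizures are also one of five features that qualify a patient for entry, under "Fever/history of fever plus one of". The seizure target has no stated start. The study window is described thus: "The duration of the intervention will be 6 hours from initial screening to the point at which attempts to meet all targets have been achieved".

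Under Use of the study results, a larger cluster randomised study will be sought if the study succeeds and the targets prove achievable.

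**The concern.** A state target is met by anyone who arrives normal and stays normal. Treatment is tied to need, but the endpoint is not, so the attainment figure mixes two groups: patients whom the bundle brought to target and patients who were there already. Three things follow.

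- **Achievability is overstated.** High attainment may say little about how often an abnormal value was corrected, yet achievability is the basis for going on to the larger study.
- **The contrast is diluted.** Patients at target on arrival score alike in both phases and add nothing to the difference.
- **Case mix leaks in.** The protocol names time and staff as confounders of its before/after design. A shift between phases in the share arriving normal moves the endpoint even if care is unchanged.

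The seizure target adds an ambiguity in the other direction: depending on when its clock starts, it may be failed before care begins.

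**Working it through.** **Inputs.** The protocol states no power, effect size or expected rate for target attainment; 200-250 is an expected accrual, split equally, so 100-125 per phase. There is no figure to reproduce. All rates below are assumptions chosen to show size and direction.

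**1. Dilution of one state target.** Let q be the share at target on arrival (assumed to stay there), and a and b the shares of the remainder corrected in phases 1 and 2. Observed attainment is q + (1−q)a and q + (1−q)b, so the difference is (1−q)(b−a).

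With q = 0.80, a = 0.25, b = 0.50:
- Phase 1: 0.80 + 0.20 × 0.25 = 0.85
- Phase 2: 0.80 + 0.20 × 0.50 = 0.90
- A 25-point gain is reported as 5 points.
- Two-sided 5% power (normal approximation): about 19% at 100 per phase in all patients; about 37% for 25% versus 50% in the 20 per phase off target. With Fisher's exact test, enumerating both binomials, these become about 14% and 27%.

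With a = 0.40 and b = 0.70 the pattern is the same:

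| At target on arrival | Difference, all patients | Power, all (100 per phase) | Power, off target only |
|---|---|---|---|
| 50% | 15 points | 72% | 87% (50 per phase) |
| 70% | 9 points | 46% | 65% (30 per phase) |
| 90% | 3 points | 17% | 26% (10 per phase) |

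In these examples restricting to patients who needed correction raises power despite the smaller numbers.

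**2. Case mix.** Hold correction at 25% in both phases and let q rise from 0.80 to 0.85. Attainment goes from 0.85 to 0.85 + 0.15 × 0.25 = 0.8875, a gain of 3.75 points with no bundle effect. That is three quarters of the 5 points that the assumed real effect produces.

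**3. Combined endpoint.** The two process targets are undiluted. If they go from 25% to 50% and the four state targets from 85% to 90%, the six-target mean goes from (2 × 25 + 4 × 85)/6 = 65% to (2 × 50 + 4 × 90)/6 = 76.7%. The gain is 11.7 points rather than 25: diluted, but not lost.

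**4. Seizures.** If a seizure at entry counts as failure and 10-40% enter with one, that target cannot exceed 90-60%, and the six-target total cannot exceed (5 + 0.9)/6 = 98.3% to (5 + 0.6)/6 = 93.3%. If the clock starts at screening, there is no such cap.

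**5. If targets were stacked as independent observations.** The ratio of true to assumed variance is [Σp(1−p) + ρ Σ sd·sd over pairs j≠k] / [6 p̄(1−p̄)], with ρ the within-patient correlation. True type I error is 2(1 − Φ(1.96/√ratio)).

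| ρ | Equal rates: ratio, type I error | Four at 85%, two at 25%: ratio, type I error |
|---|---|---|
| 0 | 1.0, 5.0% | 0.65, 1.5% |
| 0.1 | 1.5, 11.0% | 0.97, 4.6% |
| 0.2 | 2.0, 16.6% | 1.29, 8.4% |
| 0.3 | 2.5, 21.5% | 1.61, 12.3% |

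One score per patient, compared by a t-test, kept simulated type I error at 4.3-5.9% across the scenarios tried.

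**The case against.** The strongest reply is that the study is a declared pilot, that each target is also reported separately, and that both phases use the same inclusion criteria. Patients normal on arrival therefore appear in both arms and do not by themselves create a spurious difference. That stands while case mix is stable, but it does not answer the dilution or the overstated attainment, and it fails if case mix shifts.

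A second reply is that keeping a patient at target is also care. Table 1 gives IV fluid to patients without shock, all patients are observed hourly, and a patient can deteriorate within six hours. This stands: patients at target on arrival should be reported as their own group, not dropped.

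Three stronger readings are tempting, and the protocol does not support them.

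- *The p-value for the combined endpoint is too small.* The protocol does not assign chi-squared to that endpoint; a per-patient score or an all-targets-met indicator fits the wording equally well. Even if targets were stacked, the error is inflated only above a break-even correlation (about 0.11 for the 85%/25% rates), below which the test is conservative. The SAP, which might settle this, was not available.
- *The combined endpoint mostly measures case mix.* The 85% versus 90% example describes a single state target. The six-target mean on the same rates is 65% versus 76.7%.
- *Patients who enter with seizures necessarily fail.* If the target runs over the six hours from screening, a patient whose seizures stopped beforehand can meet it.

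**Conclusion.** The concern holds for the four state targets and, through them, for the combined endpoint in diluted form. The two one-hour process targets are unaffected. As worded, the primary endpoints credit the bundle with patients who needed no correction, remove from each state target's between-phase difference a fraction equal to the share already at target, and leave the comparison open to a shift in arrival case mix. At an assumed 80% on target at arrival, a 25-point gain in correction shows as 5 points, and a 5-point shift in case mix alone shows as 3.75. These sizes rest on assumed rates and on patients at target staying there; the direction does not depend on the particular values. Inflated type I error is only a conditional risk, whose direction depends on the correlation and on how far target rates differ. This should be corrected, but it does not invalidate the study.

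**What to change.** Amend the endpoint and analysis wording as follows.

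- Score the two time targets in all patients.
- For each state target, report *corrected within 6 hours* among those off target at first observation and *maintained* among those at target, and give the size of each group. Compare phases stratified by, or adjusted for, arrival status.
- Start the seizure target at screening, so that seizures before entry do not count as failure.
- List the targets that enter the combined endpoint, given six targets and eight components. Define it as one score per patient (targets met divided by targets applicable) and compare phases at patient level, for example with a Wilcoxon test, or GEE with the patient as cluster.
- Reconcile the saturation figures in Tables 1 and 2: a reading of 93-94% misses the target without meeting the oxygen trigger.

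The cost is mainly wording. Admission finger-prick glucose is planned for all subjects, study nurses chart regular observations in both phases, and Table 2 names a seizure chart. The sponsor should confirm that saturation, repeat glucose and seizures are charted in Phase 1 as in Phase 2. The downside is smaller denominators for individual targets, so some will support description only.

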***Secondary (to be measured at day 10 and day 40)***

1. Death
2. Persistent seizures requiring treatment
3. Significant neurological disability
4. Functional ability
5. Evidence of persistent renal injury
6. Blood and CSF bacterial load of *S. pneumoniae*

Death will be measured as a composite secondary endpoint (days to death/last known alive) using the following methods:

*Day 10 (acute)* – date of discharge (alive) or date of death will be recorded up to 10 days of inpatient antibiotic therapy.

*Day 40 (convalescent)* - Final outcome recorded ‘alive or dead’ following records from follow up or response to mobile telephone at until 6 weeks.

A history of seizures and functional ability since discharge will be taken, and endpoints 3-5 will be measured formally using the ***Modified Rankin score***, serum creatinine (to calculate eGFR), blood pressure and urine dip (for protein).

| **Urine** | Dip for proteinuria (5mls) |  |
| **Nasal swab** | Culture for *S. pneumoniae* and genotypic exploration of micro-evolution between the nose/blood and CSF of *S. pneumoniae* | 1 swab |

**iv.iv Methodology to address specific objective 4: Quantification of the *S. pneumoniae* bacterial load**

Serum and remainder CSF (following diagnostic procedures) will be removed from each subject with informed consent and stored at -80°C in the MLW laboratory. The diagnostic CSF algorithm will be followed for the study (appendix1). All samples that are gram stain/culture positive for *S. pneumoniae* or inflammatory but culture negative will undergo DNA extraction and Real-Time PCR using pneumolysin primers with TAMRA fluorescent probes. Standards will be generated using synthetic pneumococcal DNA (Eurofins, USA).

These results will be added to the trial database and analysed with outcome comparing survivors and non survivors between phases 1 and 2.

**iv.v Methodology to address objective 5: Further research use of remaining samples**

Specific permission will be requested from each participant during the formal informed consent process for the further use of any remaining tissue samples. We plan to analyse these samples in a future series of experiments to explore the host immunological response to the pathogen *S. pneumoniae*, including measurement of markers of apoptosis and complement activation, based on work at LSTM (31). [name] laboratory at the LSTM is currently studying the host immunology of pneumococcal disease, with an aim to novel protein vaccine design. A recent analysis of the CSF and serum samples from a previous meningitis trial in QECH, the steroids in adult meningitis (SAM) trial (1) has shown that there is massive complement consumption within the CSF compartment in ABM (work currently un-published). This is previously un-described in meningitis and may indicate a novel aspect of pathogenesis. Samples from this study would be used in experiments to explore complement consumption further. We will also request permission from the participants for the use of genetic material (RNA) to be analysed (both from bacteria cultured and from the host), in a series of collaborative experiments studying gene expression in ABM with and Imperial College. A large proteomic analysis of CSF samples from the SAM trial failed to identify any biomarkers of disease severity (31). We plan to analyse gene expression in the serum and CSF, to identify if severity is due to gene over or under-expression, and to use this approach to identify disease severity biomarkers and guide further proteomic work. A material transfer agreement is attached for this work. Recent work from [name] at Imperial College using gene expression has shown an important genetic basis for meningitis in Europe due to *Neisseria meningitidis*(32). No studies to date have studied this in meningitis due to *S. pneumoniae*, or used gene expression to identify patterns of disease susceptibility in resource limited settings. All additional research work under objective 5 using stored samples from this study is aimed at understanding the very high mortality from ABM in Africa, and with the long term aim of designing appropriate vaccines and adjunctive therapies to improve outcome within Africa. All samples will be stored for a maximum of 5 years. Where laboratory technology permits, the majority of this work is planned to be done in Malawi, providing capacity building, training and educational support to local staff and adding to the research profile of Malawi.

**Summary of sample storage and disposal.**

| **Sample** | **Storage** | **Duration** | **Disposal** |
| --- | --- | --- | --- |
| Blood | MLW -80oC freezer and  LSTM -80oC freezer if samples moved under a MTA. Stored for future related projects with full consent of study participants | Stored up to 5 years after the end of the project. | Usual Category II waste procedure according to University of Liverpool/Liverpool School of Tropical Medicine protocol |
| **Sample** | **Storage** | **Duration** | **Disposal** |
| CSF | MLW -80oC freezer and LSTM -80oC freezer if samples moved under a MTA for further related collaborative research studies with full consent of study participants. | Stored up to 5 years after the end of the project. | Usual Category II waste procedure according to University of Liverpool protocol/ Liverpool School of Tropical Medicine protocol |

**iv.vi Recruitment and follow up**

**Recruitment**

Subject recruitment in both phases will be entirely within the Adult Emergency and Trauma Centre (AETC) at Queen Elizabeth Central Hospital (QECH). Subjects will be recruited between 8am and 4pm by a team of 6 study nurses based in AETC. The nurses will screen all unwell triaged patients by the inclusion criteria and recruit, following verbal assent, all adults with suspected ABM.

Based on 9 years (2001-9) of data from MLW, it is expected that 50-100 cases of proven ABM will be recruited per 6 months, and a total of 1-2000 potential trial participants will be screened. Flexibility is built into the study timeline to allow for slower/delayed recruitment, particularly during the introduction of the bundle in phase 2.

**Follow up**

All participants who have been included based on CSF results will be followed up on the medical ward during their inpatient stay. Each participant will be reviewed daily and clinical progress data will be collected by the PI, the study clinical officer or one of the study nurses. The results of blood tests performed by the inpatient medical team will also be collected by download from the Spine recording system. For more detail on Spine please see data confidentiality on page 23.

All included subjects from Phases 1 and 2 surviving to discharge from hospital will be followed up weekly for 6 weeks (40 days) by text message sent to a nominated mobile phone (with consent from the participant). At six weeks each surviving participant will be invited to a study outpatient appointment at QECH. The outpatient follow up clinic will be staffed by the PI and the study clinical officer. Clinical data will be collected in outpatients to inform the secondary endpoints of the study.

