**Transport**

Study subjects will be asked to come back to outpatient follow up at 6 weeks from discharge. Expenses will be paid for this. Where a subject is unable to attend follow up for personal, geographical or financial reasons, attempts to collect data over the telephone will be made.

Staff leaving work at the end of the late shift will be driven home by taxi, funded from the study budget to enable secure and safe travel after hours.

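### The day-10 and day-40 endpoints have no stated day 0, and late follow-up is timed from discharge, so the outcome windows move with length of stay

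*Protocol*

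**What the plan says.** Section iv.ii (Endpoints) lists death, persistent seizures, neurological disability, functional ability and renal injury among the secondary endpoints, all to be measured at day 10 and day 40. It does not say from which date the days are counted.

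- **Form of the death endpoint:** "Death will be measured as a composite secondary endpoint (days to death/last known alive) using the following methods". So a dated event is intended, not only a status.
- **First time point, the acute one at day 10:** the rule reads "date of discharge (alive) or date of death will be recorded up to 10 days of inpatient antibiotic therapy".
- **Second time point, the convalescent one at day 40:** vital status only, ascertained "following records from follow up or response to mobile telephone at until 6 weeks". No origin is given for the six weeks.

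Section iv.vi (Follow up) says that patients "surviving to discharge from hospital will be followed up weekly for 6 weeks (40 days) by text message". It goes on to the clinic visit: "At six weeks each surviving participant will be invited to a study outpatient appointment at QECH". The origin of that visit is stated outright only under Requirements, in the Transport paragraph: "Study subjects will be asked to come back to outpatient follow up at 6 weeks from discharge". Section iv.ii also takes the seizure and functional history from discharge onwards.

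The Data analysis section compares the phases with simple mortality proportions, chi-squared and Fisher tests of fixed endpoints, logistic regression and Kaplan-Meier analysis.

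**The concern.** A proportion dead by a fixed day is comparable between groups only if every patient is observed over the same interval. Here the interval labelled day 40 appears to end a fixed time after discharge, so it lengthens by one day for each day in hospital. The interval labelled day 10 is cut short for anyone discharged alive before day 10.

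Length of stay comes after the intervention and may be affected by it, for example through faster recovery or more early survivors. It may also change between two calendar periods for unrelated reasons such as bed pressure. The phases are sequential and not randomised, and the Protocol already acknowledges confounding by time. A window tied to discharge adds a further difference between phases that could be avoided.

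The mortality comparison is the second specific objective, and the Sustainability section makes the writing of local guidelines conditional on a mortality benefit. For the outcomes measured at the clinic, the time allowed for recovery before assessment also varies with stay.

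**Working it through.** **1. The plan's own figure.** Follow up equates 6 weeks with 40 days. 6 × 7 = 42, so the figure does not reproduce; it is 2 days short.

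**2. When the assessments fall, counted from arrival.** Late assessment = length of stay + 42. Acute window = the smaller of length of stay and 10, taking 10 days of inpatient therapy as about 10 days from arrival. The Protocol gives no lengths of stay, so those below are assumed.

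| Assumed stay (days) | Acute window closes | Late assessment | Days beyond a true day 40 |
|---|---|---|---|
| 3 | day 3 | day 45 | 5 |
| 10 | day 10 | day 52 | 12 |
| 21 | day 10 | day 63 | 23 |

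If 40 days is meant in place of six weeks, each late assessment moves 2 days earlier (43, 50, 61). The dependence on stay is unchanged.

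**3. Possible bias in the late mortality comparison.** Only a difference in stay between phases matters. With proportion alive S, daily hazard h late in follow-up and difference in mean stay d, the shift in phase mortality is about S × (1 − exp(−h × d)).

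- S = 1 − 0.54 = 0.46, from the 54% mortality in the Executive summary. Treating this as survival at about day 40 is an assumption.
- h = 0.002 to 0.004 per day and d = 4 days, both assumed.
- Low: 0.46 × (1 − exp(−0.008)) = 0.46 × 0.0080 = 0.0037, or 0.4 percentage points.
- High: 0.46 × (1 − exp(−0.016)) = 0.46 × 0.0159 = 0.0073, or 0.7 percentage points.

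A wider range takes 46% alive at discharge, h = 0.001 to 0.005 and d = 2 to 10, with survival first carried forward 40 days: 0.46 × exp(−40h) × (1 − exp(−h × d)). This gives 0.09 to 1.84 percentage points.

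**4. Set against the precision of the study.** The Sample size section expects 200 to 250 subjects in equal phases, so 100 to 125 per phase. With 54% mortality in both, the 95% half-width for the difference is 1.96 × √(2 × 0.54 × 0.46 / n). That is 13.8 points at n = 100 and 12.4 points at n = 125. The 0.7-point shift is about 6% of the smaller half-width (0.73 / 12.4 = 0.059).

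**5. What the planned data can repair.** Weekly contact to discharge + 42 days always runs past day 40 from arrival. A patient discharged on day 4 has a first weekly text at about day 4 + 7 = 11, which would settle day-10 status. Vital status at a true day 10 and day 40 can therefore be derived where contact succeeds and dates of death are obtained. A Rankin score, creatinine or urine dip taken on day 45 in one patient and day 63 in another cannot be re-timed.

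**The case against.** The strongest reply is that the death endpoint already holds most of the remedy. It is defined as days to death or last known alive, dates of death and discharge are recorded, and Kaplan-Meier curves comparing the phases are planned. Ascertainment that runs past day 40 does not force later deaths into a day-40 count, and the choice of time zero for the curves could sit in a statistical analysis plan that is not shown. This stands, and it limits the consequence for mortality. It does not remove the conflict, because the Protocol itself sets the time points in three places that do not agree.

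Several stronger readings are tempting and are not supported:

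- **That a patient discharged on day 4 counts as alive at day 10 whatever follows.** The rule records a date of discharge alive, not a day-10 status, and weekly texts (with consent) could detect a later death. What is missing is a statement that such deaths count towards day 10. Since the rule refers to 10 days of inpatient therapy, very early discharge may also be uncommon.
- **That the Protocol times late mortality from discharge.** Only the clinic visit is explicitly timed that way. For death the origin is inferred from the Follow up wording.
- **That deaths after day 40 will enter a day-40 proportion.** The Data analysis section does not say so.
- **That a longer window is itself a bias.** Twelve extra days in both phases alike do not bias the comparison; only a difference in stay between phases does.

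It is also fair that follow-up procedures are identical in both phases, that the primary endpoints concern targets within the 6-hour intervention and are unaffected, and that the study describes itself as a pilot. Identical procedures tied to discharge still give different windows if stay differs. A visit six weeks after discharge is a legitimate choice for disability, but not under the label day 40.

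**Conclusion.** The point holds as a defect in endpoint definition that should be corrected, with modest consequences for mortality. Day 0 is not named, 40 days and six weeks are treated as equal, the acute record can close before day 10, and the late assessment falls at about length of stay plus 42 days.

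The likely mortality bias is about 0.4 to 0.7 percentage points over all patients, and 0.1 to 1.8 over a wider range of assumptions. Stay, the difference in stay between phases and the hazard after discharge are all assumed, as none is in the Protocol, and the direction of the bias is unknown. It is small beside a half-width of 12 to 14 points and can largely be recovered from dated deaths. A reader might infer that the mortality comparison is invalid; the documents do not support that. The lasting loss is in the disability, function, seizure and renal outcomes, whose timing relative to arrival cannot be restored afterwards.

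**What to change.** Reword section iv.ii, the Follow up section and the Transport paragraph so that they agree:

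- Define arrival in the emergency centre (AETC) as day 0 for every patient.
- Define death at day 10 and at day 40 from arrival, whether or not the patient has been discharged. Use dates of death and the existing weekly texts for those already at home, and state that a date is sought for any death reported by telephone.
- Read both mortality figures from a Kaplan-Meier curve that starts at arrival and is censored at last contact.
- Reconcile 40 days with six weeks.
- If the clinic remains six weeks after discharge, label it as such, use it for the non-mortality outcomes only, and record days since arrival at each visit.

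The cost is minor rewording and a little extra analysis. No extra visits are needed and clinical management does not change.
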